**S2: Study Protocol v4 (13.09.2021)**

Study questions

*1. If practicing yoga, learning the Bhagavad Gita, or combining both reduces psychological distress, then participants in these intervention groups will show significant reductions in GAD7 scores over time compared to their baseline scores.*

*2. If the interventions are more effective than no intervention, then the GAD7 scores will be significantly lower in the intervention groups compared to the control group at post-intervention assessments.*

*3. If learning the Bhagavad Gita results in more lasting stress reduction than practicing yoga alone, then the Gita group will have lower GAD7 scores at the delayed post-intervention assessment than the Yoga group.*

*4. If combining yoga and the Bhagavad Gita has a synergistic effect, then the Yoga+Gita group will experience greater immediate and sustained reductions in GAD7 scores than either intervention alone.*

*5. If no significant changes occur in the control group over time, then the GAD7 scores in the control group will remain relatively stable across all assessments.*

*6. If the interventions differ in their sustained effectiveness, then the Gita and Yoga+Gita groups will have significantly lower DPI-GAD7 scores compared to the Yoga group at 45 days post-intervention.*

*7. Gender may moderate the effect of the interventions on psychological distress.*

*8. Educational attainment may moderate the effect of the interventions on psychological distress.*

*9. If continued practice of the interventions is important for sustained stress reduction, then participants who continue practicing the interventions will have lower GAD7 scores at the delayed post-intervention assessment than those who do not continue.*

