**Analysis Plan**

Statistical models

*Descriptive Statistics:* Before any inferential tests, we will compute descriptive statistics (mean ± standard deviation for continuous variables and frequencies/percentages for categorical variables) to describe the demographic characteristics (age, gender, education level) and baseline GAD7 scores for each group.

*Tests for Normality:* To determine the appropriate statistical tests, we will first assess the normality of the GAD7 scores using the Shapiro-Wilk test. If the data are normally distributed, we will proceed with parametric tests. If the data do not meet normality assumptions, we will use non-parametric alternatives.

*Primary Plan (Parametric Tests):*

Within-Group Comparisons: To examine changes in GAD7 scores over time (Baseline, Immediate Post-Intervention, and Delayed Post-Intervention) within each group, we will use repeated-measures ANOVA. If significant, we will conduct pairwise t-tests with Bonferroni correction to compare GAD7 scores between each pair of time points (e.g., Baseline vs. IPI-GAD7, Baseline vs. DPI-GAD7).

Across-Group Comparisons: To compare GAD7 scores between the four groups (Control, Yoga, Gita, Yoga+Gita) at each time point (Baseline, IPI-GAD7, DPI-GAD7), we will use one-way ANOVA. If significant differences are found, we will apply Tukey’s HSD for post-hoc pairwise comparisons between groups.

Subgroup Analysis (by Gender, Educational Attainment, and Continued Practice): For subgroup analyses, we will use two-way ANOVA to assess whether gender (male, female), education level (Bachelor’s vs. Master’s or higher), and continued practice (yes, no) influence GAD7 score changes over time or interact with the interventions.

Effect Size Calculations: Partial eta-squared (η²) will be calculated for repeated measures ANOVA and η² will be calculated for one-way ANOVA to estimate the effect sizes.

*Backup Plan (Non-Parametric Tests):*

Within-Group Comparisons: We will use the Friedman Test to compare GAD7 scores over time within each group (Baseline, IPI-GAD7, DPI-GAD7). If significant, we will perform pairwise comparisons using the Conover Test to identify specific differences between time points.

Across-Group Comparisons: To compare GAD7 scores across the four groups at each time point, we will use the Kruskal-Wallis Test. If significant, we will conduct the Dunn’s Test for pairwise group comparisons.

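### Study questions 1 and 5 rest on within-arm tests against baseline and are not tied to the planned comparison with control, so a change common to all arms can be reported as an intervention effect

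*Protocol*

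**What the plan says.** Under Study questions, question 1 makes within-arm change the expected sign that the interventions work: "participants in these intervention groups will show significant reductions in GAD7 scores over time compared to their baseline scores". Control is not part of that criterion. Question 5 reads: "If no significant changes occur in the control group over time, then the GAD7 scores in the control group will remain relatively stable". It gives no margin for stability.

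The matching tests are under Analysis Plan, Statistical models. For change over time "within each group, we will use repeated-measures ANOVA", followed by "pairwise t-tests with Bonferroni correction to compare GAD7 scores between each pair of time points". The backup route has the same structure: "We will use the Friedman Test to compare GAD7 scores over time within each group".

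A comparison with control is planned as a separate item. Question 2 predicts that "the GAD7 scores will be significantly lower in the intervention groups compared to the control group at post-intervention assessments". To compare the four groups "at each time point (Baseline, IPI-GAD7, DPI-GAD7), we will use one-way ANOVA", with Tukey's HSD afterwards, or Kruskal-Wallis and Dunn on the backup route.

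The Variables section names GAD7 at all three visits as the primary outcome. No visit or contrast is singled out as primary, and question 1 is not made to depend on question 2.

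**The concern.** A within-arm test against baseline cannot separate the effect of an intervention from anything else that moves scores over the same period. The Sampling Plan recruits healthcare workers because of pandemic stress and measures them from 12 November 2021 to 3 January 2022. The course of the pandemic and repeated completion of the same scale could shift all four arms together. The untreated control arm is there to remove such shifts, but question 1 does not use it.

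Question 5 has the converse problem. A non-significant test in one small arm shows that no change was detected. It does not show that there was none.

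What is at stake is the claim the trial may make. Question 1 comes first in the list and can be answered yes when the interventions do nothing. With no comparison named primary, that answer could be reported as efficacy even if question 2 is negative.

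**Working it through.** **Inputs from the protocol.** SD 3.78, minimum clinically important difference (MCID) 4 points, power 80%, alpha 0.05 (Sample size); two-sided testing (Analysis Plan); 1:1:1:1 allocation (Sampling Plan). The protocol gives no sample size, so there is no stated figure to reproduce.

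**Implied size.** The normal approximation gives 2 × (1.960 + 0.842)² × (3.78/4)² = 14.02, so 15 completers per arm. A two-sample t-test gives 15.04, so 16. With Bonferroni for six pairs the t-test gives 24. I use 16 and show 15 and 24 as the range.

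**Assumptions not in the protocol.** Within-person correlation r from 0.3 to 0.7, equal for all pairs of visits; normal scores; the same fall in all four arms at both later visits, so the true intervention effect is zero.

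**Rule simulated.** In each arm, repeated-measures ANOVA at 0.05. If significant, paired t-tests at 0.05/3 each. A reduction is counted if either later visit is significantly below baseline. The arms are independent, so with per-arm probability p:
- at least one of three intervention arms: 1 − (1 − p)³
- all three: p³

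**Results, 16 per arm, common fall of 2 points** (20,000 simulated trials per setting; other simulation runs differ by about a percentage point):

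| r | p | At least one arm | Control ANOVA not significant |
|---|---|---|---|
| 0.3 | 0.316 | 1 − 0.684³ = 0.68 | 0.60 |
| 0.5 | 0.445 | 1 − 0.555³ = 0.83 | 0.46 |
| 0.6 | 0.546 | 1 − 0.454³ = 0.91 | 0.36 |
| 0.7 | 0.686 | 1 − 0.314³ = 0.97 | 0.23 |

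- Requiring all three arms, r = 0.6: 0.546³ = 0.16.
- Common fall of 1 point, r = 0.6: at least one arm in about 36%.
- No common fall: at least one arm in about 4%. The excess therefore comes from leaving out control, not from multiplicity.
- Planned between-arm one-way ANOVA at the immediate post-intervention visit, same 2-point fall: about 5% at every correlation.

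**Range over sample size, 2-point fall, r = 0.3 to 0.7.** At least one arm: 65% to 95% with 15 per arm, 88% to over 99% with 24. Control read as stable: 64% down to 25% with 15, 43% down to 8% with 24.

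**Precision available for question 5.** The SD of a change is 3.78 × √(2(1 − r)). At r = 0.6 this is 3.38. The 95% CI half-width with 16 completers is 2.131 × 3.38/√16 = 1.80 points. At r = 0.3 the SD is 4.47 and the half-width 2.38 points.

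Only the parametric route was simulated. The Friedman route also tests each arm alone, so the same reasoning applies.

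**The case against.** The strongest reply is that the comparison with control is already planned. Question 2 compares the arms after the intervention. Under randomisation a shift common to all arms cancels, so the test is valid without an arm-by-time term or baseline adjustment, and the roughly 5% rejection rate bears this out. This stands. A reader might infer from question 1 that the trial has no valid test against control; the protocol does not support that.

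Question 1 is also worded as a prediction: if the interventions work, reductions will be seen. It is not an explicit rule that a reduction proves efficacy. This stands in part. The question offers no other criterion, its test is within-arm, and nothing subordinates it to question 2.

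Two further inferences go too far.
- A reader might suppose that the plan claims a difference when an intervention arm is significant and control is not. No section combines questions 1 and 5 in that way, so an error rate for that pairing would describe a rule the protocol does not contain.
- A reader might count regression to the mean as built in. Entry requires no minimum GAD7 score, so the protocol does not show score-based selection. Stressed staff may volunteer more readily, but that is conjecture.

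Finally, the rates depend on the assumed common fall, the correlation and whether one arm or all three must show a reduction. That is true, and it is why ranges are given.

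**Conclusion.** The point holds as a flaw in how questions 1 and 5 are framed and tested. It does not mean that the trial lacks a randomised comparison. Question 1 can be answered yes with zero intervention effect whenever scores fall in every arm, and the protocol does not prevent that answer from being presented as efficacy.

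The at-least-one-arm rate of 68% to 97% is conditional on a common fall of 2 points, half the stated MCID, and on the assumed 16 completers and correlations. Smaller falls, or requiring all three arms, bring it down substantially. The direction does not depend on these assumptions: a within-arm test responds to any common change and the between-arm test does not. For question 5, a true drift of half the MCID passes as stability often enough that non-significance cannot support the claim.

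This should be corrected. Because question 2 already supplies a valid test at both post-intervention visits, it does not undermine the trial as a whole.

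**What to change.** 1. State that efficacy is judged only by the between-arm contrast with control at the immediate and delayed post-intervention visits, as in question 2. Preferably adjust for baseline GAD7 (ANCOVA, or one model with arm and visit); the adjustment mainly gains precision.
2. Reword question 1 so that within-arm changes are descriptive, with 95% confidence intervals and no efficacy claim, on both the parametric and the backup route.
3. Replace question 5 with the control-arm change and its 95% CI. Call control stable only if the whole interval lies inside a pre-stated margin smaller than the 4-point MCID. With a half-width of about 1.8 to 2.4 points at 16 completers (correlation 0.6 and 0.3), a tight margin may be out of reach. In that case drop the stability claim and report the estimate.

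The cost is the wording of two study questions, a sentence in the Analysis Plan and one covariate. No additional data or participants are needed.

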**Sampling Plan**

Existing Data

*None*

Data collection procedures

*Population:* The participants will be healthcare workers (HCWs) employed at Sri Jagannath Heath Care and Research Centre, Dhanbad, Jharkhand, India. They are facing significant psychological stress during this COVID-19 pandemic, making them suitable candidates for the study aimed at assessing interventions for stress reduction.

*Recruitment:* Participants will be recruited by posting a call for participation on the internal email system and notice board of the hospital. This announcement will include all relevant information about the study, such as the nature of the interventions, expected commitment, and the informed consent form. No payments will be provided for participation.

*Inclusion and Exclusion Criteria:*

Inclusion Criteria: Participants will be aged 18 years or over and be currently employed HCWs at the hospital. They will also need to be available for the entire duration of the intervention (1 week) and follow-up (45 days post-intervention).

Exclusion Criteria: Participants with pre-existing diagnosed mental health conditions will be excluded to ensure that the study focuses on measuring the effect of the interventions on psychological distress caused by work-related stress during the pandemic, rather than on pre-existing disorders.

*Grouping:* After the eligible HCWs return the signed informed consent forms, they will be randomized into one of four groups (Control, Yoga, Gita, Yoga+Gita) using a chit-pull system, as previously described, in a 1:1:1:1 ratio.

*Study Timeline:* Recruitment will begin on October 25, 2021, and end on November 5, 2021. The baseline assessment (B-GAD7) will be administered on November 12, 2021. The interventions (Yoga, Gita, Yoga+Gita) will be conducted between November 13, 2021, and November 19, 2021. The immediate post-intervention GAD7 (IPI-GAD7) will be collected on November 20, 2021 (1 day post-intervention). The delayed post-intervention GAD7 (DPI-GAD7) will be administered on January 3, 2022 (45 days post-intervention).

*Intervention Details:* Participants in the intervention groups will attend daily 1-hour sessions for one week. The Yoga group will practice yoga for the entire hour. The Gita group will attend Bhagavad Gita lessons for one hour. The Yoga+Gita group will have 30 minutes of yoga followed by 30 minutes of Bhagavad Gita lessons. The Control group will not receive any intervention.

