*Data Collection Process:* Psychological distress will be measured using the Generalized Anxiety Disorder-7 (GAD7) scale at three time points; Baseline (B-GAD7) - Administered before the interventions starts, Immediate Post-Intervention (IPI-GAD7) - Administered 1 day after the last intervention session, and Delayed Post-Intervention (DPI-GAD7) - Administered 45 days after the intervention. All data will be collected anonymously using only the participant identification numbers (PINs) to maintain confidentiality.

*Data Management:* The consent forms and a document linking participants’ names to their PINs will be securely stored and not accessible to the data analysis team or to the intervention coordination and data collection team. The data will include GAD7 scores and demographic information (age, gender, education level).

Sample size

*The sample size will be calculated to detect significant effects with 80% power to detect a minimum clinically important difference of 4 for the GAD7 with a standard deviation of 3.78 at the standard alpha error of 0.05. A dropout rate of 15% will be considered. PASS 2020, v20.0.6 will be used to calculate the sample size.*

Stopping rule

*None*

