**Variables**

Manipulated variables

*None*

Measured variables

*The primary outcome variable is psychological distress, measured using the GAD7 scale at baseline, immediately post-intervention, and 45 days post-intervention. The main predictor variable is the intervention type (Control, Yoga, Gita, Yoga+Gita), and demographic covariates (age, gender, education) will also be collected. Continued practice is a follow-up variable to examine its impact on long-term outcomes.*

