Subgroup Analysis (by Gender, Educational Attainment, and Continued Practice): For the gender, education, and continued practice subgroup analyses, we will use the Mann-Whitney U Test to compare GAD7 scores between subgroups at each time point.

Effect Size Calculations: We will compute the Kendall’s W for effect size in the Friedman test and η² for the Kruskal-Wallis test to estimate the effect sizes. Statistical Significance: For all tests, a two-tailed p-value < 0.05 will be considered statistically significant.

Transformations

*None*

Data exclusion

*Participants who miss any follow-up session (B-GAD7, IPI-GAD7, DPI-GAD7) will be excluded.*

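### Question 9 treats a self-chosen, post-intervention comparison as showing that continued practice matters, and the planned tests neither account for earlier scores nor restrict it to the active arms

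*Protocol*

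**What the plan says.** Question 9 in the Protocol's list of study questions makes the importance of continued practice depend on whether "participants who continue practicing the interventions will have lower GAD7 scores at the delayed post-intervention assessment than those who do not continue". The Variables section gives the variable the same causal reading: "Continued practice is a follow-up variable to examine its impact on long-term outcomes".

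Two analyses are named in the Analysis Plan, under Subgroup Analysis:

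- **Parametric plan.** A two-way ANOVA, in one sentence with gender and education, asks whether "continued practice (yes, no) influence GAD7 score changes over time or interact with the interventions".
- **Non-parametric backup.** For the same three variables, "we will use the Mann-Whitney U Test to compare GAD7 scores between subgroups at each time point".

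Neither analysis adjusts for B-GAD7 or IPI-GAD7, and neither is limited to the active arms. The Variables section gives intervention type four levels, one of them Control. Under Intervention Details in the Sampling Plan, "The Control group will not receive any intervention".

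**The concern.** Gender and education are fixed before randomisation. Continued practice is not: participants choose it after the last session on 19 November 2021, when they already know how they feel. If people who are doing better are likelier to go on, continuers will look better on 3 January 2022 whether or not practice helps. Randomisation gives no protection, because practice is not randomised.

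Two further difficulties follow from the text. Control participants have nothing to continue, so their place in a yes/no split is undefined. Testing at each time point also takes in baseline (12 November) and the immediate assessment (20 November, one day after the last session). Continuation cannot have affected the former and can hardly have affected the latter.

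At stake is the reading of question 9: earlier response, or in one version of the backup test the arm effect, could be reported as a benefit of practice.

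**Working it through.** The Protocol gives no sample size or power figure for question 9, so there is nothing of its own to reproduce. The check asks how often the planned comparison would be significant if practice had no effect.

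**Inputs from the Protocol.** SD 3.78, difference of 4 points, 80% power, two-sided 0.05, four arms 1:1:1:1. For scale, a two-group comparison needs 2 × (1.96 + 0.84)² × 3.78² / 4² ≈ 14.0, so 15 per arm; the t-based figure is 15.04, so 16.

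**Assumptions not in the Protocol.** 16 analysed per arm, all correlations between assessments 0.6, about half of active participants continue, selection at log-odds 0.5 to 1 per SD, a 4-point effect in each active arm, and zero effect of practice.

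**1. Selection on a better IPI score, raw DPI-GAD7, active arms.** Let g be the correlation between the propensity to continue and a better IPI score. With half continuing, the two groups differ by 2 × 0.798 × g = 1.596g SDs at IPI. Of that, 0.6 carries to DPI: 1.596 × 0.6 × 3.78 × g = 3.62g points. For g = 0.3 this is 1.09 points and for g = 0.5 it is 1.81. Simulation at log-odds 0.5 to 1 agrees: spurious difference −1.0 to −1.8 points, Mann-Whitney rejection 14–38%. With 30 per arm and g of 0.3 to 0.5, rejection is 26–60%. With g = 0 it stays at 4–5%.

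**2. Change scores.** The parametric plan speaks of changes over time, so this matters. In SD units:

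- Selection on IPI, baseline-to-DPI change: cov(IPI, DPI − B) = 0.6 − 0.6 = 0, so no bias.
- Selection on IPI, IPI-to-DPI change: cov(IPI, DPI − IPI) = 0.6 − 1 = −0.4. Continuers start low and regress upward, so the bias runs against them (+0.7 to +1.2 points).
- Selection on improvement, raw DPI: cov(B − IPI, DPI) = 0.6 − 0.6 = 0, so no bias.
- Selection on improvement, baseline-to-DPI change: cov(B − IPI, B − DPI) = 1 − 0.6 − 0.6 + 0.6 = 0.4, so the bias favours continuers.

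Simulated two-sided rejection with no practice effect:

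| Analysis, active arms | Continuing follows better IPI | Continuing follows improvement |
|---|---|---|
| Raw DPI | 14–38% | about 5% |
| Baseline-to-DPI change | about 5% | 11–29% |
| DPI regressed on practice, arm, B-GAD7, IPI-GAD7 | about 5% | about 5% |

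**3. Control coded as not continuing, backup test.** Let continuation be random. With n per arm, the non-continuers are n controls and 1.5n active participants, so controls make up n / 2.5n = 0.4 of them. The arm effect leaks in as 0.4 × 4 = 1.6 points, and rejection is about 30%. An arm term in the model removes this leak but not the selection in step 1.

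**4. Four arms by practice.** The design has 8 cells, but Control/continued is empty, so the rank is 7 and the full interaction cannot be estimated.

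**5. Limit of adjustment.** Suppose an unmeasured trait drives both continuing and the scores. Adjusting for arm and IPI-GAD7 then lowers the rate of falsely finding continuers better (nominal 2.5%) from 22–54% to 8–18% with 15 per arm, and from 40–84% to 13–33% with 30 per arm. It does not restore the nominal rate.

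**The case against.** The strongest reply is that the Protocol does not mistake the nature of the variable, that question 9 is the last of nine and sits under subgroup analysis, and that the numbers rest on assumed mechanisms. Much of that stands, and it rules out several stronger readings that a reader might infer:

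- *That practice is declared a baseline variable.* It is not; the Variables section calls it a follow-up variable. The fault is that it then gets the same tests as gender and education.
- *That Control will be counted as not continuing.* This is nowhere stated. The Study Timeline lists the interventions as the three active arms, and question 9 concerns people who continue them, so an active-arms analysis is a natural reading. Selection and pooling together give 63–85% rejection, but that figure needs the unstated coding and applies only to the backup test. Coding details may also sit in an analysis plan not at hand.
- *That any planned analysis would be biased towards practice.* Step 2 shows that change scores can be unbiased, or biased against continuers.
- *That comparisons at baseline and IPI are worthless.* As tests of a practice effect they mean nothing, but they can reveal prior differences. Under selection on IPI, the Mann-Whitney test at IPI flagged the difference in 35–83% of simulated trials.

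What the reply does not meet is that the Protocol itself names the tests and words the conclusion causally. Neither planned test protects against selection under both plausible mechanisms.

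**Conclusion.** The point holds and should be fixed, but it does not threaten the trial's main results. With no practice effect, the comparison for question 9 can reject about 14–38% of the time on raw DPI-GAD7 or about 11–29% on baseline-to-DPI change, according to which mechanism operates. These figures rest on the assumptions listed in the working. That a bias can arise needs only that continuing is related to how participants were already doing; its size and direction depend on the mechanism and the score.

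The Control issue is conditional. If Control is left out, it disappears and the selection problem remains. If Control is coded as not continuing in the backup test, rejection is about 30% even with random continuation.

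A reader might go on to doubt the arm comparisons. The document gives no ground for that: they are randomised and do not use continued practice.

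**What to change.** - For question 9, use the three intervention arms only. Regress DPI-GAD7 on continued practice, adjusting for arm, B-GAD7 and IPI-GAD7. This replaces the two-way ANOVA and the Mann-Whitney test for continued practice.
- Keep any comparison of continuers and non-continuers at baseline and IPI as a descriptive check for prior differences, not as a test of practice.
- Reword question 9, and the matching sentence under Variables, as an exploratory association. Adjustment reduces selection but may not remove it where unmeasured traits are involved.

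The cost is some wording and one regression on variables that the Protocol already collects. The downside is a weaker claim for question 9.
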